**FHI 360**

**Hormonal Contraception and the Risk of HIV Acquisition: An Individual Participant Data Meta-Analysis**

**(HC-HIV Meta-analysis)**

**(NICHD award number R21HD069192/ FHI 360 Study # 10263)**

**Detailed Statistical Analysis Plan**

# INTRODUCTION

This study is a meta-analysis of individual participant data (IPD) from 18 prospective longitudinal studies. The main aim of the IPD meta-analysis is to determine whether hormonal contraception, including combined oral contraceptives (COCs) and the progestin-only injectables DMPA and Net-En increase women’s risk of acquiring HIV infection. We will compare the rate of HIV acquisition among women who use COCs, DMPA and Net-En with the rate among women who do not use hormonal contraception. This statistical analysis plan is an extended version of the statistical analysis plan from *HC-HIV IPD Meta-Analysis Protocol - Statistical Analysis Plan 0.95*. This analysis plan provides details on analysis strategy, variable construction and statistical testing procedures.

# STUDY OBJECTIVES

We will investigate the following objectives:

1. To determine whether use of different hormonal contraceptives (COCs, DMPA and Net-En, separately) increases the risk of HIV acquisition compared to women not using hormonal contraception.
   1. To determine whether use of different hormonal contraceptives (COCs, DMPA and Net-En, separately) increases the risk of HIV acquisition among young women (ages 15-24 years).
   2. To determine whether use of different hormonal contraceptives (COCs, DMPA and Net-En, separately) increases the risk of HIV acquisition among older women (ages 25-49 years).
   3. To evaluate whether HSV-2 infection status (across both age groups) modifies the effect of hormonal contraception (DMPA, COCs, and Net-En, separately) on the risk of HIV acquisition and to determine whether different hormonal contraceptives increase the risk of HIV acquisition among HSV-2 negative and HSV-2 positive women.
2. To compare the risks of HIV acquisition among the three hormonal contraceptive groups (DMPA, OC and Net-En users).

# EXPOSURES AND OUTCOMES

## Exposure variable

The primary exposure of interest is hormonal contraceptive use, specifically the use of low-dose COCs (including estrogen plus progestin), and the injectable progestins DMPA (150 mg depot medroxyprogesterone acetate administered IM every 3 months) and Net-En (200 mg norethisterone enanthate administered IM every 2 months). COCs, DMPA and Net-En use will be measured as time-varying exposures during a number of consecutive visit segments (e.g. every 3 months). No washout period will be considered for DMPA and Net-En use because most studies do not collect specific injection dates.

Our primary comparison group, a non-hormonal (NH) group, will be women not using hormonal contraceptives during the interval between study visits and will be comprised of women not using any modern contraceptive method, women using condoms (either consistently or inconsistently), sterilized women, and women using intrauterine devices (IUDs) or diaphragms.

## Outcomes

The primary outcome variable is incident HIV infection. This will be defined as a new HIV infection following a visit where the participant was HIV negative. The criteria for HIV diagnoses are those defined by the investigators of the individual studies and are typically based on a positive ELISA/rapid test confirmed by a positive Western blot or HIV PCR test. The midpoint between the last negative and first positive HIV test will be used as the estimated HIV infection date.

## Censoring

Study participants will be censored at the time they report using a non-study method (such as the progestin-only pill or high dose COCs) or at the end of the study or at the last follow-up visit before 30 months of the study. Though some studies did not distinguish low dose COCs from the progestin-only pill or high dose COCs, we will conduct sensitivity analyses based on those studies that have and have not specified low dose COC use during the study period.

## Data imputation

In principle, missing data won’t be imputed for the data analysis. However, due to the nature of the study design and time-varying contraceptive use, we will impute contraceptive use between visits by carrying forward across visits contraceptive data if the data was collected through questions concerning method use at the current visit. Similarly, we will impute the contraceptive use between visits by carrying backward across visits contraceptive data if the data was collected with questions concerning contraceptive method use in the past. Similarly, this imputation approach will apply to other key confounders such as condom use and high-risk sexual behaviors.

# ANALYSIS METHODS

The following sections describe the statistical methods that will be used to investigate the objectives. We will use descriptive statistics and statistical tests to examine between-study heterogeneity and univariable and multivariable methods for the analysis of IPD.

## Descriptive Analysis

We will conduct descriptive analyses before proceeding to meta-analyses to gain a detailed understanding of the data received within and between studies. Descriptive statistics will be used to summarize study participant baseline characteristics for each study, region and overall. Those baseline characteristics will include

- Socio-demographic characteristics
  - Age
  - Education
  - Marital status/living with partner
  - Employment (Yes/No)
  - Sexual worker (Yes/No) or exchange sex for money/gifts
- Number of live births
- Condom use
  - Any condom use (any condom use, no condom use, no sex)
  - Condom use for primary partner
  - Condom use for other partner(s)
  - Condom use for unspecified partner(s)
  - Condom use with last sex
- Contraceptive use (COC, OC unspecified, DMPA, Net-en, injectable unspecified, implant, non-hormonal)
- Sexual behavior
  - Age at first sex
  - Coital frequency in past month
  - Anal sex (Yes/No)
  - Number of lifetime partners
  - Number of partners in past 3 months
  - New partner
  - Concurrent partner
- Primary partner information
  - Partner had HIV
  - Partner had another partner
  - Partner had nights
- STI/RTIs
  - Chlamydia infection
  - Gonococcal infection
  - Trichomonas infection
  - BV
  - Vaginal discharge/cervicitis
  - Candida vaginitis
  - HSV-2
  - Genital ulcer (clinician diagnosed)
- Vaginal practice
  - no practice/water (fingers only)
  - soap
  - cloth/tissue/cotton wool
  - other practices besides soap or cloth/tissue/cotton wool
- Self-reported symptoms
  - Itching
  - Abnormal discharge
  - ulcer

Categorical variables or continuous variables that have been categorized will be summarized by frequencies and percentages and analyzed using Cochran-Mantel-Haenszel tests across study groups and sites. Data recorded for continuous variables will be summarized by medians and ranges and analyzed by Wilcoxon Mann Whitney tests among the study groups and/or sites.

## Assessment of confounding

Assessment of confounding is a critical aspect of this meta-analysis as it clear that women that choose different methods of contraception likely differ in respect to sexual behavior, condom use, etc. For this reason having adequate information on possible key confounding variables as part of study datasets is part of the study inclusion criteria and also is part of our assessment of bias, which guides some sensitivity analyses.

In addition to the possible confounding factors that have been pre-specified by researchers (age, marital status/living with partner, condom use, number of sexual partners), the following factors will be examined, if information is available in all/most datasets:

Demographic and sexual behavioral variables related to the individual participant:

- Recent sexual behavior (concurrent sex partners, coital frequency);
- Study site/region

Partner-related variables representing a woman’s risk of sexual exposure to HIV:

- Primary partner’s recent sexual behavior (number of sex partners, partner had other partners, had commercial sex, condom use);

Variables that attempt to measure a woman’s susceptibility to HIV infection:

- Sexual and health behaviors (anal sex, oral sex, vaginal practices);
- Reproductive health factors (parity, pregnancy history and status, lactation status);
- Physical exam variables (cervical ectopy, genital epithelial findings)
- Presence of cervical infections (CT, GC) and vaginal infections (bacterial vaginosis, trichomoniasis, vulvovaginal candidiasis)

We will measure and examine for confounding by factors that either increase a woman’s risk of exposure or susceptibility to HIV infection, and which may also be differentially distributed among contraceptive use exposure groups. Each potential confounding factor will be included and excluded in the Cox Proportional Hazards model for each individual study along with HC exposures and the pre-specified covariates (above) to evaluate the change in the hazard ratios associated with HC exposure. If a greater than 10% change occurs in the hazard ratios for the contraceptive exposure variables results with inclusion of the potential confounder, the variable will be considered for inclusion in the final models of COC, DMPA and NET-EN use and HIV infection in the meta-analysis.

## Effect modification

Though a priori hypotheses about age (younger vs. older) and HSV-2 infection (not infected vs. infected) status will be addressed individually in the meta-analysis, the question of whether age and HSV-2 infection status modify potential relationships between hormonal contraception and HIV infection is still of interest. We will evaluate their modification effect on the hormonal contraception and HIV acquisition relationship by adding an interaction term between age and HC, and between HSV-2 and HC using Cox proportional hazard models for each individual study and overall. The modification effect for age and HSV-2 infection status will be evaluated in separate models. If p<0.05 for the likelihood ratio test comparing models with and without the interaction term, statistical evidence of interaction (i.e. effect modification) between the contraceptive exposure variable and HIV will be concluded.

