## Meta-analysis

We will conduct meta-analysis of individual participant data using both one- and two-stage meta-analysis approaches in each age group and combined, and for studies that provided HSV-2 information (1). Each method has advantages and disadvantages. When both methods are used, they can provide valuable complementary information.

We will use two-stage meta-analysis as our primary approach to examine the overall association between HC exposures and HIV acquisition. Using this method, participants in each study are compared directly only with other participants in the same study. The two-stage method is well suited to assess between study heterogeneity. While the method is less suitable for identifying prognostic factors (due to the different sets of covariates measured across datasets), it is possible to assess effect modification.

The one-stage method combines and analyzes data from all studies as if they belong to a single study. Study identity is included in statistical models to take into account the fact that the data are from different studies. The one-stage method might not be a valid option if there is marked heterogeneity between the studies. We will explore the effects of confounding and effect modification using the one-stage method. If there is statistical evidence of confounding, we will include the confounding variables in the two-stage multivariable analysis.

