### One-stage Meta-analysis

We will first use the stratified Cox proportional hazard regression to examine the overall unadjusted associations. This allows the survival curve to differ arbitrarily between studies, while assuming that hazard ratios for the exposures of interest are the same across studies. This result will be compared to the overall effect estimated by the univariable analysis from the two-stage meta-analysis. We will then construct multivariable Cox models (3) stratified by study that include identified confounding factors and/or have been pre-specified in the study protocol (age, marital status/living with partner, condom use, and number of sexual partners), and summarize the HC exposure effects on HIV acquisition. Random effects Cox proportional hazard regressions with studies as clusters will also be conducted for univariate and multivariable analyses. This can be seen as a multilevel model with two levels, which allows the estimation of effects of interest in relation to both study-level and participant-level covariates. The effect of modification between HC and age and HSV-2 infection, respectively, will be examined using the approaches proposed above.

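### The overall contraceptive × age and contraceptive × HSV-2 tests do not separate within-study from across-study information, so their error rate can exceed 5% when studies differ in both effect and case mix

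*SAP*

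**What the plan says.** - **Test.** SAP, Effect modification: an interaction term is added "using Cox proportional hazard models for each individual study and overall", separately for age and HSV-2. The decision rule is "If p<0.05 for the likelihood ratio test comparing models with and without the interaction term".
- **Method.** SAP, Meta-analysis: "We will explore the effects of confounding and effect modification using the one-stage method". The same section says of the two-stage method that women are compared only with others in their own study, and that "it is possible to assess effect modification". It gives no rule for pooling study-specific interactions. It also warns that the one-stage method may not be valid under marked heterogeneity, but attaches no criterion.
- **First one-stage model.** SAP, One-stage Meta-analysis: a Cox model stratified by study, "while assuming that hazard ratios for the exposures of interest are the same across studies".
- **Second one-stage model.** Same section: "Random effects Cox proportional hazard regressions with studies as clusters will also be conducted for univariate and multivariable analyses", described as a two-level model "which allows the estimation of effects of interest in relation to both study-level and participant-level covariates". The SAP does not say whether the random effect is on the baseline hazard, on the HC effect or on both.
- **Interaction in these models.** The section closes by referring the age and HSV-2 interactions back to the methods already described, without choosing between them.
- **Premise of the primary analysis.** SAP, Two-stage Meta-analysis: the true hazard ratios are taken to follow a distribution, so they differ between studies.

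**The concern.** In a one-stage model with a common HC effect, the interaction coefficient combines two contrasts. The first compares the HC effect in younger and older women of the same study. The second compares the HC effect in studies with many young women and studies with few. The second is ecological: any study-level reason for a different HC hazard ratio can appear as age modification. The SAP itself names region, sex-worker population and background incidence as possible sources of heterogeneity. The same applies to HSV-2.

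There are two consequences. If the HC effect is related to case mix across studies, the interaction is biased. If it is unrelated, the interaction is unbiased but varies more than the model allows, and the likelihood ratio test is too liberal.

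The stake is largest for HSV-2, because Objective 1.3 asks whether HSV-2 status modifies the effect, and Table 1 marks the analysis by HSV-2 status as primary. A reported modification could then reflect which studies enrolled which women.

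**Working it through.** **Figure to reproduce.** The SAP states only the 5% level. It gives no event counts, no between-study SD of the HC effect (τ, on the log hazard ratio scale) and no age or HSV-2 mix. The 18 studies are from the Introduction; all other inputs are assumptions.

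**Assumptions.** K = 18 studies; 100 infections each (1,800 in all); share on the method q = 0.4; mean modifier share m = 0.5 with between-study SD s = 0.10 or 0.20; τ = 0, 0.2 or 0.3; correlation ρ between a study's modifier share and its log hazard ratio of 0 or 0.5. No study has any true interaction.

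**Approximation for the common-HC-effect model.**

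1. Sampling variance of the interaction: V = 1/[1800·q(1−q)·m(1−m)] = 1/(1800 × 0.24 × 0.25) = 0.00926, so SE = 0.096.
2. Fraction of the information that comes from across studies: f = s²/[m(1−m)]. For s = 0.20, f = 0.04/0.25 = 0.16. For s = 0.10, f = 0.01/0.25 = 0.04.
3. Spurious log ratio of hazard ratios: the across-study slope ρτ/s times f, which is ρsτ/[m(1−m)]. For s = 0.20, ρ = 0.5, τ = 0.2: 0.5 × 0.20 × 0.2/0.25 = 0.08, a ratio of 1.08. For τ = 0.3: 0.12, a ratio of 1.13.
4. Variance that the model ignores: f²τ²(1−ρ²)/(K·s²). For s = 0.20, τ = 0.3, ρ = 0: 0.0256 × 0.09/(18 × 0.04) = 0.0032.
5. False rejection: the probability that a normal variable, with the mean from step 3 and variance V plus step 4, lies outside ±1.96 × 0.0962 = ±0.189. For s = 0.20, τ = 0.3, ρ = 0 the SD is √(0.00926 + 0.0032) = 0.112, so the limit is 0.189/0.112 = 1.69 SDs, giving 9.1%.

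**Comparison with simulation** (Poisson counts by study, modifier and method, equivalent to a study-stratified constant-hazard Cox model, or a normal approximation to the study estimates; 1-df test; 1,000 to 1,500 runs where listed separately):

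| s | τ | ρ | By hand | Simulated |
|---|---|---|---|---|
| 0.20 | 0 | – | 5.0% | 4.7–5.1% |
| 0.20 | 0.2 | 0 | 6.8% | 5.9% |
| 0.20 | 0.3 | 0 | 9.1% | 7.7–9.1% |
| 0.20 | 0.2 | 0.5 | 14.7% | 12.7–15% |
| 0.20 | 0.3 | 0.5 | 26.5% | 21.6–24.1% |
| 0.10 | 0.3 | 0 | 6.0% | about 6% |
| 0.10 | 0.2 | 0.5 | 7.4% | about 8% |
| 0.10 | 0.3 | 0.5 | 10.4% | 10–10.7% |

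The hand formula runs slightly high when the link is strong.

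**Sensitivity to case mix** (4,000 runs, share on the method varying from 20% to 60%, τ = 0.3). Modifier share 30–50%: 5.4% unlinked and 7.5% at ρ = 0.5. Share 20–70%: 8.5% and 18.6%. Share 5–95%: 15.3% and 43.6%. With the same mix in every study there is no inflation at any τ up to 0.5 (1,000 runs).

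**Within-study information only.** With study-specific HC effects, false rejection is 4.7–5.9% in every 4,000-run scenario.

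**Random-effects alternative.** A random baseline alone still leaves one HC effect for all studies, so the mechanism above is unchanged. With a random HC effect (s = 0.20, 1,000 runs), rejection for common effect / random HC effect / within-study only is:
- τ = 0.3, ρ = 0: 7.7 / 5.3 / 4.6%
- τ = 0.2, ρ = 0.5: 13.8 / 7.6 / 5.8%
- τ = 0.3, ρ = 0.5: 21.6 / 6.6 / 4.6%
- τ = 0.3, ρ = 0.8: 37.6 / 11.1 / 6.0%

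**Would the SAP's heterogeneity rule catch it?** Take a typical within-study variance of 1/(100 × 0.4 × 0.6) = 0.0417. Then I² ≈ τ²/(τ² + 0.0417). For τ = 0.2 this is 0.04/0.0817 = 49%, just inside the SAP's lowest class, where no further investigation follows. For τ = 0.3 it is 0.09/0.1317 = 68%.

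**The case against.** A reader might infer that the overall tests certainly come from the common-HC-effect model and that false modification will be declared well above 5%. The SAP does not support either statement.

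- **The model is not fixed.** The common-hazard-ratio sentence introduces the unadjusted stratified model. Random-effects Cox models follow, and the interaction sentence comes after both and refers to approaches in the plural. If the random effect is on HC, most of the inflation goes. This stands. However, the SAP does not say that it is, and a random HC effect leaves a residual when case mix and effect are linked (6.6–7.6% at ρ = 0.5, 11.1% at ρ = 0.8).
- **The size rests on inputs that the SAP does not give.** This also stands. Without real heterogeneity, or with a narrow and unlinked mix, the rate stays at about 5–6%. The larger figures need a correlation that has been assumed. The illustration also uses one method and one degree of freedom, whereas the SAP has three exposures.
- **Guards exist.** The warning about marked heterogeneity and the I² classes would prompt further work at τ = 0.3. Neither is tied to the interaction test, and τ = 0.2 passes under the 50% threshold.
- **Within-study evidence is already planned.** The per-study interaction tests are unaffected by this problem. What is missing is a rule that pools them and gives them priority.
- **Age modification is not a listed objective.** Objectives 1.1 and 1.2 ask about risk within each age group, and the SAP treats age modification as a further question of interest. The point therefore weighs more for HSV-2.

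**Conclusion.** The concern holds in a conditional form. The SAP assigns the overall interaction tests to the one-stage method and nowhere separates within-study from across-study information. Under the stratified model with a common HC effect, or a random-effects model with a random baseline only, the likelihood ratio test can exceed its 5% level if both the HC effect and the age or HSV-2 mix differ between studies. Under the stated assumptions (s of 10–20 points, τ of 0.2–0.3), the rate is about 5–9% with no link and about 8–23% at correlation 0.5. A random HC effect lessens this but does not remove the ecological part. The common-effect assumption also conflicts with the distribution of true hazard ratios on which the primary two-stage analysis rests.

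The documents do not show that the actual error rate will be high, because neither the heterogeneity nor the spread of case mix is given. This is a should-fix, most relevant to Objective 1.3.

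**What to change.** In the SAP sections Effect modification and One-stage Meta-analysis, state that:

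1. Conclusions on overall effect modification rest on within-study information only. The simplest route is to take the interaction log ratio of hazard ratios from each study's own Cox model, already planned, and pool these by random effects.
2. If a one-stage estimate is also wanted, it uses study-specific HC effects, or centres the modifier at its study mean with a separate term for the across-study association.
3. The random-effects Cox model specifies whether its random effect is on the baseline hazard, the HC effect or both.
4. The interaction from the common-HC-effect model is descriptive only.

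**Cost.** A few sentences and little programming; the participant data needed are those already being analysed. The interval widens somewhat. In the illustration the standard error rises from 0.097 to 0.105 (0.105/0.097 = 1.08, about 8%); the hand formula gives √[1/(1 − 0.16)] = 1.09. Studies with sparse data will contribute little or nothing, mainly for Net-En, for which the SAP expects fewer data. Pooling is preferable there, since study-specific HC effects for three methods in 18 studies could need up to 3 × 18 = 54 coefficients.

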## Pregnancy

The issue of how to analyze women who become pregnant during the follow-up period is complicated since pregnancies that occurred are directly related to HC exposure and clearly have an impact on subsequent HC exposure. In addition, some studies censored women from their studies after a pregnancy occurred. Several analyses will be conducted. As the primary analysis, we will censor study participants after their last non-pregnant visit (i.e., after the last visit before they become pregnant). We note however, that since pregnancy is an outcome directly related to HC exposure and may be related to HIV acquisition, excluding or censoring women with pregnancy might bias the relationship between HC exposure and HIV acquisition. In addition, we will conduct two sensitivity analyses for evaluating the impact of the pregnancy on the HC-HIV acquisition relationship. First, we will include pregnancy as a time-varying covariate in a Cox regression analysis model. Second, we will conduct an analysis where we exclude women who ever became pregnant during any of the studies from the analysis population and reanalyze the data. The person-time between these sensitivity analyses and the primary data analysis method will also be evaluated.

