### Sensitivity Analyses

Though this meta-analysis provides high quality individual participant data and valuable information about the exposure effect of HC on HIV acquisition, our approach has some limitations. First, the validity of the results of the meta-analysis is dependent on the risk of bias in the component studies. While the IPD meta-analysis can help avoid problems associated with the analyses and reporting of the component studies, it cannot eliminate bias due to their study design or conduct. For example, systematic differences between participants’ characteristics in the HC exposure groups may occur in the component studies resulting in imbalances in prognostic factors associated with HIV acquisition. In addition, due to the variety of study designs, not all the subgroups and potential confounding variables are available in all component studies. It is also possible that we may be unable to recode variables appropriately across studies. Together, these factors could potentially limit our ability to control for confounding and residual confounding could occur. In addition there are fewer Net-En data available in the component studies than there are data for COCs and DMPA.

We will perform the following sensitivity analyses to examine the robustness of the results of our meta-analyses (Table 1):

1. Based on the risk of bias in HC exposure data, we will stratify and analyze data/studies separately by the following criteria
   1. where data/studies cannot distinguish between progestin-only injectables and implants,
   2. Where data/studies cannot distinguish between Net-En and DMPA injectable contraceptives,
   3. Where data/studies cannot distinguish between COC and POP oral contraceptives.
2. Based on the assessment of the risk of bias of the component study – stratify studies with and without an identified risk of bias (e.g. studies that have retention rates lower than 80% at one year).
3. Based on HC exposure switching – censoring participants at the visit before the first contraceptive method switch.
4. Based on pregnancy status
   1. Include pregnancy as a time-varying covariate (ie. not censoring women at the time of pregnancy)
   2. exclude women who are ever pregnant from the analysis
5. Based on key confounding or risk factor variables – stratify studies that do not measure key confounders in a time-varying manner (e.g. participant risk factors, condom use).

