### Supplementary Analyses

We will apply the approaches mentioned above to conduct the following supplementary analyses (see Table 1) based on:

1. Condom use: We will conduct an analysis of our primary objectives among the subset of women that report no condom use during the study period.
2. High vs. low incidence study populations: We will conduct a stratified analysis of the HC and HIV association based on stratifying studies with high vs. low HIV incidence in the non-hormonal contraceptive group (using the median as the cutpoint).
3. Women by region (Eastern Africa, Southern Africa and South Africa)
4. Age groups among young women: If there are sufficient numbers of HIV cases among 15-24 year old age group, we will conduct an analysis for the primary objectives based on finer age groups: 15-20 years and 21-24 years (versus women > 25 years).

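### The ever-pregnant exclusion and, if read at woman level, the no-condom subset select women on later events, so their hazard ratios can move from the null with no true effect

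*SAP*

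**What the plan says.** The Pregnancy section of the SAP sets three treatments of pregnancy.

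- **Primary:** "we will censor study participants after their last non-pregnant visit". Woman-time before the pregnancy is kept.
- **First sensitivity analysis:** pregnancy enters the Cox model as a time-varying covariate.
- **Second sensitivity analysis:** "exclude women who ever became pregnant during any of the studies from the analysis population". Sensitivity Analyses, item 4, repeats it as "exclude women who are ever pregnant from the analysis", and Table 1 lists it.

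The same section says that "pregnancies that occurred are directly related to HC exposure and clearly have an impact on subsequent HC exposure" and warns that "excluding or censoring women with pregnancy might bias the relationship between HC exposure and HIV acquisition". It plans to compare person-time across the analyses. It does not say whether a pregnancy after HIV infection counts towards the exclusion.

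Supplementary Analyses, item 1, repeats the primary objectives "among the subset of women that report no condom use during the study period". It does not say whether non-use is judged per woman over all her follow-up or per visit segment. Under Exposure variable, condom users belong to the non-hormonal (NH) comparison group.

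**The concern.** Being never pregnant, or never reporting a condom, over the whole of follow-up is known only at the end of follow-up. A woman whose counted time stops early because she acquires HIV has had less chance to fail the criterion. An uninfected woman followed towards the 30-month limit has had more chance, and when she fails, all her earlier woman-time goes too. The retained set is therefore enriched for cases. If the disqualifying event is commoner in one contraceptive group, the enrichment is unequal and the hazard ratio (HR) shifts even when neither pregnancy nor condoms affect HIV.

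The ever-pregnant exclusion sits among the analyses meant to examine robustness. A shift produced by selection could be read as a finding about the primary HR, or could hide a real one.

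**Working it through.** **Inputs.** The SAP gives no HIV incidence, pregnancy rate or condom-reporting rate, so there is no figure to reproduce. From the SAP come the selection rules, the Cox HR of hormonal contraception (HC) against NH, and the 30-month limit. All rates below are assumptions.

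**Closed form, ever-pregnant exclusion.** Let HIV hazard be λ, pregnancy hazard r, follow-up T years and a = λ + r. Risks are independent, groups fixed, the true HR is 1.0, and pregnancies are counted only up to infection. Per woman enrolled:

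- retained cases = (λ/a)(1 − e^(−aT))
- retained woman-years = λ[(1 − e^(−aT))/a² − T·e^(−aT)/a] + T·e^(−aT)

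Take λ = 0.04, T = 2 and pregnancy 15 (NH) against 3 (HC) per 100 woman-years.

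- NH: a = 0.19, e^(−0.38) = 0.684; cases 0.0666, woman-years 1.430, rate 4.65 per 100.
- HC: a = 0.07, e^(−0.14) = 0.869; cases 0.0747, woman-years 1.812, rate 4.12 per 100.
- Rate ratio = 4.12/4.65 = 0.89.

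In NH the rule keeps 0.0666/(1 − e^(−0.08)) = 87% of cases but e^(−0.30) = 74% of non-cases. In HC it keeps 97% and 94%.

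Other settings, with λ = 0.04:

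| Follow-up | Pregnancy per 100 woman-years, NH vs HC | Rate ratio |
|---|---|---|
| 1 year | 10 vs 3 | 0.97 |
| 2 years | 15 vs 3 | 0.89 |
| 2.5 years | 20 vs 5 | 0.82 (Cox HR by simulation 0.83) |

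**Censoring instead.** Cases are (λ/a)(1 − e^(−aT)) and woman-years (1 − e^(−aT))/a, so the rate is λ in both groups and the ratio is 1.00.

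**Simulation with Cox models** (2 million women per scenario, HIV 2 to 10 per 100 woman-years). With 2.5 years of follow-up and pregnancy rates from 10 vs 2 up to 30 vs 2, the exclusion gave 0.91 down to 0.70. With staggered follow-up it gave 0.80 to 0.95. With fixed follow-up, a true HR of 1.5 became 1.04 to 1.36. HIV incidence hardly mattered.

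**When the pregnancy bias vanishes or reverses.**

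- Equal pregnancy rates: 1.00 to 1.02.
- Pregnancies after infection also counted, over as long a period as in uninfected women: 1.00 to 1.02. Partial counting helps partly. In the 15 vs 3, 2-year case the ratio is 0.91 with 3 months of observation after infection, 0.93 with 6 months and 0.97 with 1 year.
- A shared log-normal risk factor for pregnancy and HIV with log-SD 0.5, 1.0 or 1.5 (HIV 5 per 100; pregnancy 10 vs 2 or 20 vs 2): the exclusion gives 0.86 to 0.93, 1.01, and 1.12 to 1.21. Censoring at pregnancy is then itself biased, at 1.03 to 1.36.

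**No-condom subset at woman level** (true HR 1.0, HIV 5 per 100 woman-years, 2.5 years). Only condom use that starts after baseline creates the bias.

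| Condom starts per year, NH vs HC | HR in never-condom subset |
|---|---|
| 0.4 vs 0.2 | 0.76 |
| 0.6 vs 0.2 | 0.58 |
| 0.3 vs 0.3 (baseline use equal or unequal) | 1.00 |
| 0.2 vs 0.4 | 1.30 |

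Censoring at the first condom report gave 0.99 to 1.00 throughout.

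**The case against.** A reader might infer that both analyses lower the HR by construction. The documents do not support that. Selection on the future is built in; its direction is not. A downward shift needs three things: more pregnancy or condom starting in NH than in HC, events counted only up to infection or shortly after, and no strong risk shared between pregnancy and HIV. The SAP fixes none of them. Its wording on pregnancy during any of the studies can be read to include pregnancies after infection, and it says pregnancy may be related to HIV acquisition.

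The pregnancy part is also partly disclosed. The SAP warns of bias, pairs the exclusion with a covariate analysis that does not select on the future, and promises cautious interpretation. The condom analysis is listed as supplementary, not as a sensitivity analysis, and could be read by visit. NH includes sterilized women and IUD users, which may narrow the pregnancy gap. Contraceptive exposure is time-varying, whereas the calculations use fixed groups; switching would probably weaken the bias.

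All of this stands and limits what can be claimed about direction and size. It does not rescue the analyses. The SAP's warning treats excluding and censoring alike, although under independent risks only exclusion distorts the HR. Comparing person-time will not reveal the mechanism. The condom item carries no warning. A check whose bias can take either sign is poor evidence of robustness.

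**Conclusion.** The concern holds in a limited form. The ever-pregnant exclusion, and the no-condom subset if applied to whole women, condition on events after time zero and can give an HR away from 1.0 with no true effect. For pregnancy, the illustrative bias at a true HR of 1.0 runs from 0.97 to 0.83, and to 0.70 under more extreme assumed rates. It assumes independent risks, more pregnancy in NH and counting only to infection. The middle case of 0.89 is an 11% shift, just above the 10% change that the SAP's Assessment of confounding treats as notable. For condoms, the assumed scenarios run from 0.58 to 1.30, so not even the sign can be claimed.

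The primary analysis censors at pregnancy and is not affected by this selection, though strong shared risk would bias it by another route. The point is worth correcting but does not threaten the main result.

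**What to change.** 1. **No-condom analysis.** State that it works on visit segments and keeps those with no reported condom use. Alternatively, take women with no condom use at baseline and censor at first reported use.
2. **Ever-pregnant exclusion.** Drop it from Pregnancy, from Sensitivity Analyses item 4 and from Table 1, and rely on the primary censoring plus the time-varying covariate analysis. If it is kept, label it as selecting on the future, state whether pregnancies after infection count, and do not use it as evidence on robustness.

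Replacing the exclusion with censoring at an estimated conception date would add little: it differs from the primary rule by about half a visit interval.

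The cost is SAP wording, some recoding of data already held by visit, and one fewer pregnancy sensitivity analysis if the exclusion is dropped. No new data are needed.
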